## Abstract

**Background:**

The volume of residual alveolar bone is critical to the survival of dental implants. When the volume of alveolar bone in the posterior maxillary region is less than 4 mm, maxillary sinus floor elevation (MSFE) with the lateral approach is an effective option. Traditionally, this standard approach is usually conducted at 4–6 months after tooth extraction (standard MSFE). However, defective dentition due to extraction can impair mastication during the period of bone remodeling, especially if the molars on both sides are severely compromised and must be extracted. MSFE before extraction (modified MSFE) can take full advantage of residual tooth strength. However, the effectiveness and practicability of the modified MSFE procedure remain unknown. Therefore, the aim of this study was to compare the clinical outcomes of modified vs. standard MSFE, in order to provide references to periodontists.

**Methods/design:**

The study cohort included 25 adult patients (50 surgery sites) recruited from Peking University Hospital and School of Stomatology who met the inclusion criteria. The two sides of each patient will be randomly divided into two groups: a test group-modified MSFE or a control group-standard MSFE. The surgical duration and patient-reported outcomes (visual analog scale for discomfort) will be documented. Clinical indicators, including implant survival rates, mucosal conditions, and complications, will be recorded every 6 months during the 5-year follow-up period. The volume of the alveolar bone and marginal bone level will be assessed radiographically (cone-beam CT and periapical films) every 6 months. Histological analysis of biopsy samples retrieved from both sides will be performed to evaluate the biological features of the bone.

**Discussion:**

The current study will explore the implant survival rates, safety, reliability, effectiveness, and practicability of the modified MSFE procedure. Moreover, the extent of osteogenesis on the sinus floor will also be assessed. The results of this trial will provide strategies for the modified MSFE procedure to achieve ideal clinical outcomes.

**Trial registration:**

International Clinical Trials Registry Platform ChiCTR1900020648. Registered on 1 January 2019

**Supplementary Information:**

The online version contains supplementary material available at 10.1186/s13063-021-05047-5.

## Background

Dental implantation is a viable option to restore impaired dentition. However, an adequate volume of residual alveolar bone is critical for the survival of a dental implant [1]. For atrophied posterior maxilla with a residual bone height of less than 4 mm, it is wise to conduct maxillary sinus floor elevation (MSFE) surgery to optimize the condition of the bone prior to implantation [2].

As is generally known, MSFE can be performed via the transalveolar or lateral approach. As compared to the transalveolar approach, MSFE with the lateral approach provides a direct view of the surgical field, minimizes the risk of perforation, and ensures an adequate volume of grafted bone material [2–4]. However, multiple intra- and postoperative complications as well as discomforts caused by this procedure remain problematic [5]; therefore, various methods have been proposed to improve impaired masticatory function during the healing period [6–10]. Previous studies have mostly concentrated on methods to shorten the healing period rather than directly improve masticatory function. Therefore, the patients may experience discomfort and impaired oral function for at least 10–14 months after surgery, especially after extraction of the molars on both sides due to severe periodontitis [11].

However, it is not reasonable to deny necessary extractions due to possible partial edentulous or loss of oral function. Even with active treatment, 40% of “hopeless” teeth do not survive for longer than 4 years on average [12]. Based on this and the high success rate of dental implants, earlier strategic extraction of hopeless teeth is considered beneficial for implant placement [13]. However, the timing of extraction is very critical. As previously reported [14], it is also necessary to fully utilize and extend the capacity of the natural tooth. Given that the integrity of dentition is fundamental to high masticatory efficiency [15], optimizing the longevity of the dentition will improve the patients’ quality of life. Since extraction and MSFE are inevitable for some patients with periodontitis, it is reasonable to ask whether it is technically and clinically feasible to extract the compromised teeth after the elevation of the sinus floor.

The reliability and the safety of extended MSFE to the apical area of the neighboring teeth, as proposed by Beitlitum et al. [16], were assessed in a recent clinical trial involving 65 patients to enable future implant placement while avoiding the need for sinus reentry after extraction of the proximal teeth. It can be inferred that MSFE can be successfully achieved prior to extraction of the corresponding teeth.

Base on the dilemma of patients with severe periodontitis and the inference above, the current research proposes MSFE before extraction. In clinical practice, we try to maintain the compromised tooth to fully utilize its residual function in order to reduce the dentition-impaired period by at least 6 months. The extraction and implantation will be completed in one visit to minimize the number of surgeries. This time is a good opportunity to investigate the promoting effect of functional stimulation on bone regeneration, which may improve conditions for implantation.

### Objective and hypothesis

The major goal of the current randomized controlled trial is to compare the clinical, radiological, histological, and patient-reported outcomes of modified vs. standard MSFE.

The primary hypothesis is that modified MSFE can achieve ideal clinical outcomes similar to those of standard MSFE, while improving mastication. Considered outcomes include implant survival rate, marginal bone remodeling, and discomfort, as assessed with a visual analog scale (VAS). Histological and radiological analyses of bone quality and quantity will also be considered.

## Methods

### Overview

The proposed study is designed as a prospective single-center, split-mouth, randomized controlled trial. We plan to recruit 25 patients with severely periodontally compromised molars on both sides and in need of dental implant treatment in the atrophied posterior maxilla. The participants will be recruited by the research staff from Peking University Hospital and School of Stomatology (Beijing, China). All procedures, recalls, and analyses will be conducted at this hospital. The study protocol was approved by the Ethics Committee of Peking University Hospital and School of Stomatology (approval no. PKUSSIRB-201840191). The study has been registered with the International Clinical Trials Registry Platform (identifier no. ChiCTR1900020648).

The systemic health status of all participants will be qualified prior to treatment. All patients recruited for the study will receive standard periodontal initial therapy and periodontal maintenance at regular intervals. Once the clinical and periodontal health of the patient is confirmed, MSFE surgery will be performed. Prior to surgery, all patients will be assessed both clinically and radiographically. Initial bone height, bone quality, and alveolar width will be assessed by cone-beam computed tomography (CBCT).

### Inclusion criteria

The following are the inclusion criteria:
Bilateral first/second molars requiring extraction due to severe periodontal disease (i.e., prognosis regarded as “hopeless” [17]) and the patient’s desire for replacement with implantsResidual alveolar bone height of the compromised teeth ranging from 1 to 3 mmAge ≥ 18 yearsHealthy maxillary sinuses with intact sinus floorsGood general healthNon-smokersSigned informed consent formGood oral hygiene and compliance with the treatment regimen

### Exclusion criteria

The following are the exclusion criteria:
Residual alveolar bone height of the compromised teeth more than 4 mmAge < 18 yearsPoor oral hygiene and uncontrolled periodontitisCurrent rhinitis, sinusitis, or a large cyst in the maxillary sinusSmokersCurrent and uncontrolled systemic diseases, such as diabetes mellitus, cardiovascular diseases, immune system diseases, severe osteoporosis, and/or blood disorders, such as coagulation disordersLong-term medication use (e.g., steroids, anti-epileptic drugs, and bisphosphonates)Inability or unwillingness to sign the informed consent form

### Recruitment

Potential patients will be recruited from Peking University Hospital and School of Stomatology. [name] is in charge of the local organization, while [name], [name], and [name] will participate in the recruitment and ensuring consent. Eligible patients will receive a written informed consent form explaining the trial process in plain words. If interested, the study background, study methods, duty as participants, biopsy collection and storage, possible impacts on daily life, potential risks, back-up treatment plans, and rules of confidentiality will be verbally explained by the researchers to each of the study participants. The study participants are allowed to ask any question related to the trial and have the right to be informed of all the details of the study. After we are certain that each patient fully understands the goals of the trial, an informed consent form must be personally signed prior to study inclusion. A flow chart of the treatment process is presented in Fig. 1. A SPIRIT (Standard Protocol Items: Recommendations for Interventional Trials) figure is presented in Fig. 2.

**Fig. 1 Fig1:**
[figure not shown]
Flow chart of the treatment process

**Fig. 2 Fig2:**
[figure not shown]
SPIRIT figure

### Allocation, randomization, and blinding

An external researcher blinded to the operations and analysis process will perform the randomization using the Randomizer for Clinical Trials web-based randomization service (Institute for Medical Informatics, Statistics and Documentation, Medical University of Graz, Graz, Austria). Each patient will be assigned a number within a corresponding envelope sealed by the external researcher and allocated to one of two groups: the test group (MSFE before tooth extraction) or the control group (MSFE after tooth extraction).

In accordance with the principle of blindness, the surgeon will have no access to the statistical analysis process. Similarly, the statistical analyst will be blinded to the interventions and groupings.

### Surgical interventions

#### Implant and bone substitute

All patients will receive Straumann BL implants with sand-blasted, large grit, acid-etched implant surfaces (Institut Straumann AG, Basel, Switzerland). Deproteinized Bovine Bone Mineral (Bio-oss®; Geistlich Pharma AG, Wolhusen, Switzerland) will be used as a bone substitute.

### MSFE

For the test group, with the exception of a few specific changes, the surgical procedure will largely mirror the method reported by Tatum [18]. The sinus elevation procedure will be performed before the extraction of the compromised tooth/teeth. Prior to surgery, the compromised teeth will be treated to eliminate inflammation of the periodontal tissue. Once the periodontal status of the compromised teeth is deemed clinically healthy (plaque index ≤ 1; no further bleeding on probing; probe depth≤ 4 mm), a crevicular incision will be made, which is designed to be extended to at least one adjacent tooth both mesially and distally. A full-thickness access flap will be prepared, and an access window (5 × 8 mm) will be created on the lateral wall of the maxillary sinus with the use of a round diamond bur under irrigation with sterile saline. The lower border of the window will be at least 3–5 mm above the floor to maintain an appropriate distance from the teeth on the site. The sinus membrane will be raised by at least 10 mm, exceeding the apical range of the tooth (both buccolingually and mesiodistally). The generated cavity within the maxillary sinus will be filled with deproteinized bovine bone mineral (Bio-Oss®). After the bone substitute is placed, an absorbable collagen membrane (Bio-Gide®; Geistlich Pharma AG) will be placed to cover the antrostomy defect. Interrupted or mattress PROLENE monofilament non-absorbable sutures (Ethicon, Inc., Johnson & Johnson International, Bridgewater, NJ, USA) will be placed to close the primary flap. All patients will receive preoperative antibiotic prophylaxis, consisting of 500 mg of amoxicillin three times daily for 7 days postoperatively. After a healing period of 6 months (prior to dental implant placement), CBCT will be performed to assess vertical bone height at the planned dental implant sites.

For the control group, the procedure will be performed 3 months after the extraction of the compromised teeth/tooth. Besides, standard MSFE will be conducted in accordance with the method described by Tatum [18].

### Implant placement

Six months after the MSFE procedure, dental implant surgery will be performed under local anesthesia. For the test group, the compromised teeth will be extracted with minimal invasion and biopsied with a hollow trephine drill (internal diameter, 2 mm; length, 6 mm) and the sample will be copiously irrigated with sterile saline before fixated in phosphate-buffered formaldehyde. The implant site will be prepared simultaneously, and the position and orientation will be restoratively driven. Straumann dental implants (diameter, 4.8 mm; length, 10 mm) will be inserted into the planned site, at an adequate depth so that the platform is 1 mm below the buccal plate. Then, the implant will be mounted with healing caps and sutured with PROLENE monofilament non-absorbable sutures (Ethicon, Inc.). To double-check the implant position, postoperative periapical radiographs will be obtained with the paralleling technique.

For the control group, a crestal incision will be made with mesial and distal buccal vertical release incisions. A full-thickness mucoperiosteal flap will be raised to expose the alveolar ridge and grafting site. Other steps of the procedure will be performed as described above.

For both groups, after 4 months of healing of the unloaded implants, a two-stage surgery will be performed under local anesthesia to replace the implant cover screws with healing abutments. After an additional month, the crowns will be placed.

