## Discussion

As previously reported [16], MSFE before tooth extraction is both safe and reliable. However, the effectiveness of this procedure to reduce discomfort remains uncertain, especially when both sides of molars are periodontally compromised and must be extracted.

In order to reduce the number of procedures, implantation is performed immediately after the MSFE procedure. At the same time, maintaining the tooth will minimize discomfort caused by defective oral function for a period of 3–4 months. We propose that this new clinical strategy will improve patient satisfaction with the procedure.

Because the loss of available bone volume is caused by resorption of the alveolar bone and pneumatization of the sinus mainly due to the loss of functional stimulation of the teeth [24], we presumed that functional stimuli will be beneficial to the outcomes of floor augmentation, both radiographically and histologically. The extent of osteogenesis will also be compared to determine whether the hypotheses will be accepted.

The results of the present study will determine if the modified MSFE procedure, including indications, detailed methods, postoperational complications, and management, is actually beneficial.

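### Five-year survival, marginal bone and mucosa compare two whole treatment strategies, not MSFE timing alone, and the design cannot accept or reject the functional-stimulation hypothesis

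*Protocol article*

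**What the plan says.** All references are to the protocol article.

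- **Control sequence.** The MSFE section says: "For the control group, the procedure will be performed 3 months after the extraction of the compromised teeth/tooth". The implant placement section adds, for both groups: "Six months after the MSFE procedure, dental implant surgery will be performed under local anesthesia".
- **Test sequence.** MSFE is done with the tooth in place. At implant surgery, "For the test group, the compromised teeth will be extracted with minimal invasion and biopsied with a hollow trephine drill", and then "The implant site will be prepared simultaneously, and the position and orientation will be restoratively driven". The Background gives this as a deliberate feature: "The extraction and implantation will be completed in one visit to minimize the number of surgeries".
- **Access.** For the control implant step the text gives a crestal incision with releasing incisions and then: "A full-thickness mucoperiosteal flap will be raised to expose the alveolar ridge and grafting site". It does not say how the test site is accessed.
- **Labels and goal.** The allocation section names the groups only by whether MSFE comes before or after extraction. The objective is to compare modified with standard MSFE.
- **Conclusions promised.** The Discussion says: "The results of the present study will determine if the modified MSFE procedure, including indications, detailed methods, postoperational complications, and management, is actually beneficial". On mechanism it says "we presumed that functional stimuli will be beneficial to the outcomes of floor augmentation, both radiographically and histologically", and that comparing the extent of osteogenesis will settle whether the hypotheses are accepted.

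**The concern.** The group labels name one difference between the sides, the order of MSFE and extraction. The procedures create a second: whether the implant is placed at the extraction visit or months later. The primary outcome (implant survival at 5 years), marginal bone and mucosal condition are all observed after both differences are in place. A poor test-side result could come from implant timing and be read as a failure of the early lift. Because the primary hypothesis expects similar outcomes, the opposite error matters too: two component effects of opposite sign could cancel and be read as showing that lift timing is neutral.

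A separate question arises for bone at 6 months. The Discussion credits any advantage to functional loading of the retained tooth. But the control side has also been through an extraction and 3 months of healing before its lift, and that could produce the same contrast.

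**Working it through.** The protocol has no figure of its own on this point to reproduce. The check is a timeline, followed by asking which outcomes lie before and after each difference between the sides.

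**1. Timeline, with MSFE at month 0**

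- Control: extraction at −3 (MSFE section), implant at +6 (implant placement section). Extraction to implant = 3 + 6 = 9 months.
- Test: extraction and implant both at +6. Extraction to implant = 0 months.

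The contrast is fixed by arm, so it is the same in 25 of 25 planned pairs. No pair has the early lift with a delayed implant, or the late lift with an implant at extraction.

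One sentence in the Discussion places implantation immediately after MSFE, which contradicts the 6 months in the implant placement section; the two must be reconciled. Taken literally it would make the control interval 3 + 0 = 3 months, still different from 0, so the point does not depend on it.

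**2. Outcomes after implant placement**

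Write T for the effect of lifting before rather than after extraction, and P for the effect of placing the implant at the extraction visit rather than later. If these add, the paired comparison estimates T + P: one estimate and two unknowns. With only two of the four combinations present, no model fitted to these data can separate them.

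Illustration, with P assumed because the documents give no value. Take T = 0 and a loss from P of 0 to 5 percentage points, the upper end being the 5.0% paired difference in the sample size section. The observed loss then equals that from P:

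- P = 0: expected failures in 25 test sites = 25 × 0.022 = 0.55, using the protocol's 97.8% survival.
- P = 5 points: 25 × (0.022 + 0.05) = 1.80.

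So implant timing could account for anything from 0 to 100% of the 5-point difference with no effect of the lift at all. Conversely, T = +x and P = −x give an observed difference of zero.

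**3. Outcomes before implant placement**

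The follow-up section puts the 6-month CBCT immediately before the implant goes in. Implant timing, and any flap raised at that surgery, come later and cannot affect it. Nor can they affect membrane perforation at the lift or graft complications up to that date. For these outcomes P drops out and T is estimated.

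T is itself composite. From month −3 to 0 the control site is an extraction site while the test site still holds a tooth; from 0 to +6 the test tooth remains and the control site is empty. Bone gain on the test side may reflect loading of the retained tooth, absence of extraction remodelling before the lift, or both. The two always occur together.

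The biopsy is taken at implant surgery after 6 months of graft healing, so placement does not alter that healing. The core does come from a just-extracted site on one side and a site 9 months after extraction on the other.

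**The case against.** The strongest reply is that the package is the intervention. The Background declares one-visit extraction and implantation part of the proposal, and the Discussion speaks of a new clinical strategy. Sides are randomised, so immediate placement is part of the treatment and not a confounder of it. This stands. A reader might infer that the survival comparison is invalid; the documents do not support that. What fails is only attribution to one component.

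Second, a reader might infer that implant timing and flap access undermine the bone findings at 6 months. They do not, since the CBCT precedes both.

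Third, a reader might infer that the test implant is placed without a flap. The article says the extraction is minimally invasive and mentions sutures, but never says that no flap is raised. Silence in a condensed article does not establish a difference, so the point rests on implant timing alone.

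Fourth, an occupied site versus an extraction site is close to the very definition of lifting before versus after extraction, and the Discussion blames bone loss mainly on lost stimulation. Avoiding the extraction phase could thus be called the hypothesised mechanism. This stands to the extent that the 6-month CBCT may be read as the effect of the order of the two steps. It does not license naming loading as the cause, because remodelling after extraction is not varied separately from loading.

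Finally, the stimulation idea is tentatively worded and is not the primary hypothesis. True, and this limits the weight of the point, but the Discussion still says the osteogenesis comparison will decide whether hypotheses are accepted.

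**Conclusion.** The concern holds in a limited form, and the change is recommended. Implant timing is completely tied to arm, at 0 versus about 9 months after extraction. Differences or similarity in 5-year survival, marginal bone and peri-implant mucosa therefore describe two whole strategies and cannot be attributed to MSFE before extraction alone. The randomised comparison of those strategies remains valid.

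For bone at 6 months, implant timing is irrelevant, but functional stimulation cannot be separated from the absence of a 3-month extraction phase before the lift. The plan to accept or reject that hypothesis is not supported.

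The conclusion assumes the intervals in the MSFE and implant placement sections are followed. No size is claimed for any component effect; the 0 to 5 point range is illustrative.

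**What to change.** - In the objective, the group definitions and the Discussion, state the comparison and the permitted conclusion as two strategies: MSFE before extraction with extraction and implant in one visit, versus extraction, later MSFE, then a delayed implant.
- Confine statements about MSFE timing to outcomes fixed before implant placement (membrane perforation, graft complications, 6-month CBCT), and read them as the effect of lifting before versus after extraction.
- Label functional stimulation exploratory, and remove the wording that the osteogenesis comparison will decide whether that hypothesis is accepted.
- Reconcile the Discussion's sentence on when implantation follows MSFE with the implant placement section.

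This changes wording only: no visit, procedure, sample size or analysis is affected. The cost is a narrower claim, since the trial could no longer credit or blame the timing of the lift for long-term implant results.
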